## Abstract

**Background:**

Prostate cancer is the most commonly diagnosed cancer in both African American and Hispanic men. Active surveillance is a treatment option for low- or very low-risk prostate cancer survivors, and lifestyle interventions have been found to reduce the disease progression and improve the quality of life for both survivors and their partners. To date, no lifestyle interventions that specifically target African American or Hispanic men and their partners exist. This protocol describes a study that tests the feasibility of a randomized controlled trial, a lifestyle intervention developed to enhance healthy lifestyle and quality of life among African American and Hispanic men on active surveillance and their partners.

**Methods:**

A mixed-method study, including a two-arm randomized controlled trial (*n* = 30 dyads in the intervention arm and *n* = 10 dyads in the control arm) and in-depth interviews, will be conducted. Intervention arm participants will receive bi-weekly health coaching calls (a total of 12 calls based on Motivational Interviewing), as well as physical activity-specific (e.g., power point slides, print materials about physical activity, and activity trackers for self-monitoring) and nutrition-specific education (e.g., two nutrition counseling sessions from a registered dietitian, print materials about nutrition, and food intake recording for self-monitoring) over 6 months. All participants will be assessed at baseline, month 3, and month 6. Blood will be collected at baseline and month 6 from the prostate cancer survivors. Finally, in-depth interviews will be conducted with subsamples (up to *n* = 15 dyads in the intervention arm and up to *n* = 5 dyads in the control arm) at baseline and months 3 and 6 to conduct a process evaluation and further refine the intervention.

**Discussion:**

If effective, the intervention may have a higher health impact compared with a typical lifestyle intervention targeting only survivors (or partners), as it improves both survivors’ (tertiary prevention) and partners’ health (primary prevention). Results from this study will provide important information regarding recruiting racial/ethnic minority cancer survivors and their partners. Lessons learned from this study will be used to apply for a large-scale grant to test the impact of the dyadic intervention in a fully powered sample.

**Trial registration:**

ClinicalTrials.gov (NCT No. 03575832) registered on 3 July 2018.

## Background

Prostate cancer (PCa) is the most commonly diagnosed cancer in both African American (AA) [1] and Hispanic men [2]. PCa incidence and mortality rates are 1.7 and 2.4 times higher, respectively, among AA men than among non-Hispanic White (NHW) men [1]. Although Hispanic men report lower PCa incidence and mortality rates than NHW counterparts [2], significant variations in the mortality rates exist by country of origin: Mexican men have lower death rates than NHW men, but Hispanic men from Puerto Rico and Cuba have higher death rates than NHW men [2]. Furthermore, poorer quality of life (QoL) has been reported by AA and Hispanic PCa survivors compared with their NHW counterparts [3, 4].

Active surveillance (AS), in which survivors’ conditions are closely monitored, is a management option for low-risk or very low-risk PCa survivors; survivors proceed to treatments (e.g., surgery and radiation therapy) when their disease is clinically progressed. AS is a safe and feasible treatment plan [5–7]. In a study that followed 5302 AS men across 18 countries, PCa mortality was < 1% at both 5 and 10 years after diagnosis [7]. Another study found that after nearly 20 years of follow-up, surgery was not associated with significantly lower PCa mortality than AS, but it was associated with a higher frequency of long-term adverse events (e.g., impotence and incontinence) than AS [8]. PCa treatments lead to long-term side effects, such as urinary incontinence, erectile dysfunction, and fatigue, which may greatly impact not only PCa survivors’ but also their partners’ QoL [9, 10]. Thus, AS has the potential to reduce the risk of overtreatment of clinically low- or very low-risk PCa.

Beyond disease progression, however, psychological issues may play a critical role in the individual’s decision about AS. For instance, anxiety and uncertainty about disease progression can make PCa survivors opt out of AS and receive unnecessary treatments; anxiety was a significant predictor of treatment receipt among AS men, even when socio-demographics, baseline clinical characteristics, and Prostate-Specific Antigen (PSA) velocity were taken into account [11]. Although the percentage of those who decided to receive treatment due to anxiety varied across studies, it was as high as 13% [12].

To date, there are no established recommendations for delaying or preventing the progression of the disease in AS men [13]. However, several preliminary studies have shown that lifestyle interventions targeting diet and exercise are promising for reducing disease progression and improving QoL. For example, in a randomized controlled trial (RCT) in which 93 AS men were assigned to a 1-year intensive lifestyle intervention group addressing diet, exercise, and stress management or a usual care control group, results showed that 0% of the survivors in the intervention group received treatment, whereas 12% of the survivors in the control group received treatment [14]. In addition, serum PSA level decreased (4%) in those in the intervention group, whereas it increased (6%) in those in the control group. At the second year follow-up, 5% of the survivors in the intervention group received active treatment, compared with 27% of the patients in the control group [15]. Further, a single-arm lifestyle intervention with 31 AS men reported that psychological distress (intrusive thoughts and avoidance) regarding PCa decreased, and mental health-related QoL enhanced 3 months from the intervention [16]. Given these benefits, the National Institutes of Health has recommended more research on the development of lifestyle and therapeutic interventions for survivors undergoing AS [17].

However, none of the studies available in the literature has specifically targeted AA or Hispanic men on AS, who probably would benefit the most from the lifestyle changes. Also, none of the lifestyle interventions has included partners, who are likely to be the main source of support for PCa survivors [18, 19]. Overall, the inclusion of partners is supported by previous works showing that people are more likely to change their behaviors if their significant others are also motivated to change [20, 21]. In addition, as partners also experience insecurity and anxiety during AS [22], lifestyle interventions reducing partners’ anxieties may empower them to be more supportive of behavior change for the survivors. The inclusion of partners is also supported among racial/ethnic minorities, given that partners of AA men play significant roles (as counselor, coordinator, and confidant) in cancer-related decision-making [23], and Hispanics value familismo (commitment, loyalty, and dedication to family) and thus may want to include family members in the health decision-making process [24] or may defer decision-making to other family members [25].

To date, only two pilot physical activity interventions have been published that included both cancer survivors and their partners [26, 27], and these interventions seemed to be feasible (adherence and retention rates were > 70%, and no adverse effects were reported) and efficacious to enhance physical activity and QoL. Although these results are promising, only a few AA and Hispanic men were enrolled in those lifestyle interventions, and therefore, it is not clear whether lifestyle interventions will be feasible for AA and Hispanic men on AS. Taken together, it is warranted to develop and implement a culturally tailored intervention that enhances lifestyle behaviors and QoL and reduces anxiety in partners, as well as AA and Hispanic men on AS.

The present study will test a lifestyle intervention, *Watchful Living*, for AA and Hispanic men on AS and their partners. The primary aim of the study is to determine the feasibility of recruiting the target participants and implementing Watchful Living. Secondary aims are to (1) evaluate the preliminary efficacy of the intervention in improving diet, physical activity, partner’s support for lifestyle behaviors, QoL, and inflammation and (2) conduct a process evaluation of the intervention.

## Methods

### Design

This is a mixed-methods study that incorporates a two-arm, pilot RCT and in-depth interviews. Specifically, a total of 40 survivor-partner dyads will be randomly assigned to either intervention arm or control arm. Participants will be assessed at baseline, month 3 (mid-assessment), and month 6 (post-intervention assessment). Dyads in the intervention arm will receive a home-based lifestyle intervention over 6 months. Those assigned to the control arm will receive a list of physical activity and healthy eating behavior resources (websites) at baseline and the same physical activity and nutrition materials that the intervention dyads receive after completing the month 6 assessment. In addition, 15 dyads from the intervention arm and five dyads from the control arm will be invited for in-depth interviews to conduct a process evaluation. The flow diagram of the trial is presented in Fig. 1.

**Fig. 1 Fig1:**
[figure not shown]
Participant flow

### Recruitment and data collection procedures

A total of 40 dyads (i.e., 80 individuals) will be recruited and randomly assigned to either intervention (*n* = 30 dyads) or control arm (*n* = 10 dyads). Participants will mainly be recruited from the MD Anderson Cancer Center (MD Anderson) and Lyndon B. Johnson hospital in the Houston, TX area with collaborations with the Department of Urology at each site. Eligible participants will be retrieved from the hospital’s electronic health records. An invitation letter with urologists’ signatures will be sent to the survivors, and approximately 10 days to 2 weeks later, survivors will receive a call to be invited to the study. Study staff will explain the study, and only survivors who are interested will be screened for inclusion/exclusion criteria via telephone. To recruit partners, research staff will ask permission to contact partners via telephone to screen their eligibility. To facilitate enrollment of dyads, eligible survivors will be asked to come with their partners to MD Anderson. In particular, if survivors were treated at MD Anderson, our study visit will be scheduled on the same day as their follow-up appointment at MD Anderson. Thus, they will not need to come to MD Anderson again only to participate in our study. For all participants, we will cover their parking expenses.

In addition, we will recruit participants from the community with help from the Center for Community-Engaged Translational Research (CCETR; Director: [name]). CCETR is an institutional research resource for investigators that maintains relationships with over 70 local and national organizations, providing a platform to assist with identifying and developing partnerships with Houston-area community organizations. For interested persons who contact us by telephone, hear a detailed description of the study, and provide oral informed consent to be screened, they will be screened for the inclusion/exclusion criteria. Those ineligible will be thanked for their time, and those eligible will be scheduled for an in-person baseline visit. As the participants will be recruited from multiple sites, block randomization will be used to ensure the same number of participants in each arm from each recruitment site.

All participants will be assessed at three time points: baseline, month 3, and month 6. Eligible dyads will attend an in-person baseline visit at MD Anderson. At this visit, study staff and research assistants will describe study procedures, complete consent forms, and collect baseline data. PCa survivors’ blood will be collected as well. Approximately a week later, the dyads in the intervention arm will receive an exercise prescription from an exercise physiologist and nutrition counseling from a registered dietitian in-person or via telephone. At month 3, the dyads will complete self-administered questionnaires at home, and blood will not be collected. At month 6, the dyads will visit MD Anderson and complete self-administered questionnaires. Blood draw again will be conducted among PCa survivors. Self-administered questionnaires will be completed either online (via RedCap) or on paper. For in-person data collection at baseline and month 6, survivors will receive a $25 gift card per visit, and partners will receive a $20 gift card per visit. For month 3, survivors and partners will receive a $15 gift card each. Participants will be anticipated to be enrolled in the study in July 2019.

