#### Analytic plans

The intervention adherence rate for each dyad is defined as the proportion of intervention sessions completed by both the survivor and partner. We will look at percentage of both survivor and partner completing a minimum of 9 out of 12 coaching calls and both nutrition counseling sessions. Feasibility of recruitment will be achieved if ≥ 30% of eligible participants enroll in the study, and ≥ 80% participants complete follow-up assessments at months 3 and 6. Feasibility of intervention adherence will be achieved if average proportion of intervention adherence rate is ≥ 0.7 (e.g., coaching calls and nutrition sessions completed by both the survivor and partner ≥ 70%).

Linear mixed models will be used when combined data from both survivors and partners are analyzed due to their correlation within couples. The primary endpoint for the efficacy of the interventions is the differences between intervention and control group in outcome changes between baseline and 6 months post baseline. Specifically, an intervention indicator will be included and tested for the difference of increase in outcomes between groups. In our data, cluster corresponds to couples and random intercepts will be used to represent the pair effects. We will also conduct analysis of covariance to compare efficacy outcomes of interest pre and post intervention between intervention and control group separately for survivors and partners. Covariates and corresponding baseline outcome will be adjusted for in the analyses. Two-sided statistical tests will be performed, and the significance level for each test will be set at 0.05 without adjustment for multiple testing. All results from the statistical tests will be interpreted as hypothesis generating rather than conclusive findings. We will additionally perform various descriptive analyses, including dyadic analyses, to characterize the sample and compare participants and those who refused/withdrew on demographic and medical factors.

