### Sample Size Justification

Our sample size of 40 dyads provides adequate statistical support to help evaluate our primary aim of feasibility. In terms of evaluating feasibility based on recruitment, if the true consent rate of eligible dyads is 85%, then there will be 88% probability for us to screen 50 couples or less to arrive at 40 couples that consent; if the true consent rate is 75%, then there will be only 26% probability for us to screen 50 couples or less to arrive at 40 couples consenting. With the chosen total study sample size of 40 dyads, the randomization ratio would then be determined by the sample size chosen specifically for the intervention arm. With a lack of data available in the literature on the adherence of the proposed intervention among racial/ethnic minority PCa patients and partners, it would be valuable to allocate more patients to the intervention arm than the control arm to allow a more accurate assessment of the intervention adherence rate (as part of the primary objective of the study).

Specifically, when the sample size is 30, a two-sided 95% confidence interval (CI) for the average adherence rate will extend 0.36 standard deviation (SD) from the observed average rate, where SD is the estimated standard deviation of the adherence rate, assuming the CI is based on the large sample z statistic. This is in contrast to the corresponding half width of the 95% CI for the average adherence rate of 0.44 SD when the number of dyads in the intervention arm is 20 (as a result of a 1:1 randomization ratio), representing a less precise estimate of the mean adherence rate. Finally, we would like to keep a control arm with a reasonable number of patients (10 as chosen) to allow assessment of preliminary efficacy of the intervention with a reasonable level of accuracy, yet as a secondary objective of the study.

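### The site-level randomization sentence prescribes equal arms, which contradicts the planned 30 versus 10 dyads and gives the 1:1 split that the sample size section rejects

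*Protocol article*

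**What the plan says.** Three places in the protocol article bear on the allocation.

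- **Arm sizes.** The Methods part of the abstract gives 30 "dyads in the intervention arm and *n* = 10 dyads in the control arm". Recruitment and data collection procedures opens with the same plan: "A total of 40 dyads (i.e., 80 individuals) will be recruited and randomly assigned to either intervention", with 30 dyads for intervention and 10 for control.
- **Allocation rule.** The same section ends by noting that recruitment runs through several sites, and that for this reason "block randomization will be used to ensure the same number of participants in each arm from each recruitment site". No other rule for making the allocation appears in the article.
- **Reason for unequal arms.** The Sample Size Justification says that, because adherence in this population is unknown, "it would be valuable to allocate more patients to the intervention arm than the control arm". It supports this with two interval widths. With 30 intervention dyads, "a two-sided 95% confidence interval (CI) for the average adherence rate will extend 0.36 standard deviation (SD) from the observed average rate". The alternative is "0.44 SD when the number of dyads in the intervention arm is 20 (as a result of a 1:1 randomization ratio", which it describes as the less precise option.

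**The concern.** An allocation rule is what a randomization list is built from. This one, as worded, describes 1:1 within each site, while the arm sizes in the same section require 3:1. The two cannot both be followed.

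At stake is the precision of the adherence estimate. Mean adherence is one of the feasibility criteria (success at 0.7 or above, under Analytic plans), and only intervention dyads contribute to it. Enlarging that arm is the whole argument for departing from 1:1. A list built literally from the site sentence would remove ten dyads from the adherence estimate and double the control arm.

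**Working it through.** **Inputs.** Total 40 dyads; planned arms 30 and 10 (abstract; Recruitment and data collection procedures). Half-widths 0.36 SD and 0.44 SD, two-sided 95%, "assuming the CI is based on the large sample z statistic" (Sample Size Justification).

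**Step 1: reproduce the plan's own figures.** The half-width in SD units is 1.96/√n.

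- n = 30: 1.96/√30 = 0.358, stated as 0.36.
- n = 20: 1.96/√20 = 0.438, stated as 0.44.

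Both agree. The sample size section is therefore internally consistent and rests on 30 intervention dyads.

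**Step 2: what the site sentence implies.** If site *s* contributes m_s dyads and the arms are equal there, each arm receives m_s/2. Summed over sites, each arm receives 40/2 = 20. The number and size of the sites do not matter. Counting people instead of dyads changes nothing either, because both members of a dyad are in the same arm: 40 people per arm is 20 dyads per arm.

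**Step 3: cost to the adherence estimate.** 0.438/0.358 = √(30/20) = 1.22, so the interval is about 22% wider.

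**Step 4: effect on the between-arm comparison.** For a dyad-level outcome with a common SD, the standard error of the difference in SD units is √(1/n₁ + 1/n₂).

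- 30 and 10: √(1/30 + 1/10) = 0.365.
- 20 and 20: √(1/20 + 1/20) = 0.316.

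The ratio is 0.316/0.365 = 0.87, so 1:1 gives a standard error about 13% smaller.

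**Step 5: can another reading save the sentence?**

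- *The same ratio at each site.* This fits 30 and 10 and may be what was meant, but the sentence speaks of the same number, not the same ratio.
- *Equal contributions from each site within each arm*, for example 15 + 15 and 5 + 5 with two sites. Block randomization cannot ensure this. It balances arms within a site and has no control over how many dyads a site recruits. If community recruitment counts as a third site, 10 control dyads cannot be divided equally by three in any case.

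**The case against.** The strongest reply is that nobody would be misled. The 30 and 10 figures appear in the abstract and at the start of the very section that holds the faulty sentence, and the Sample Size Justification names 1:1 and argues against it. Whoever builds the list would have to override all of that to arrive at 20 and 20. This largely stands: the intended ratio is clear, and the wider interval arises only if the sentence is taken literally. It does not remove the contradiction, because the sentence is the only allocation instruction given and it states the wrong ratio.

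A second reply is that 1:1 is not simply worse, since it improves the between-arm comparison (step 4). That is correct. But the protocol makes preliminary efficacy a secondary objective and chose adherence precision over it, so the gain does not serve the priority it set.

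Two stronger readings are tempting, and the article does not support them. One is that the unit of randomization is confused because the sentence says participants. Dyads are named as the randomized unit under Design and again under Recruitment and data collection procedures, and the word does not alter the arithmetic. The other is that the blocking factor is left out of the models. Analytic plans says only "Covariates and corresponding baseline outcome will be adjusted for in the analyses" and does not list the covariates, so site is not excluded. A statistical analysis plan that is not shown may name it.

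**Conclusion.** The contradiction is real and limited to one sentence. Read literally, it gives 20 and 20 dyads instead of 30 and 10, and an adherence interval of 0.44 SD instead of 0.36 SD on each side, about 22% wider. The offsetting gain is a between-arm standard error about 13% smaller, on an objective the protocol ranks second.

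The adherence figures use the protocol's own large-sample formula. The between-arm figure assumes a dyad-level outcome with a common SD. Both take all randomized dyads as observed.

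A reader might infer that the trial will be, or was, randomized 1:1. The article does not support that: everything else in it points to 3:1, and a wording error is the most likely explanation. The sentence still needs correcting, because the allocation ratio is a core design feature and a list cannot satisfy both statements.

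**What to change.** Replace the sentence with: *Dyads will be randomized 3:1 (intervention:control) in permuted blocks, stratified by recruitment site.* Use block sizes that are multiples of 4, so that each complete block holds the 3:1 ratio; ten complete blocks of four give 30 and 10. If a list already exists, check that it was generated at 3:1 within site.

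The cost is one sentence and a setting in the randomization system. Sites whose recruitment does not fill the last block may move the final split by a dyad or two from 30 and 10. Smaller blocks keep this shift small.

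Adjusting for site in the efficacy models is an optional recommendation. The article gives no site-level recruitment numbers, so whether 10 control dyads would support a site effect cannot be judged from it.
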